### Data management and validation

Audit data for evaluation of the training package will be managed and validated locally, before being sent to the PEARLS Central Office. Survey participants will be identified and consented locally and the 10-12 day questionnaire and prepaid envelope will be given by ward staff prior to the woman's discharge from the postnatal ward. The three month questionnaire will be sent directly from the PEARLS Central Office, to women who consented and responded at 10-12 days. All completed questionnaires will be returned to the PEARLS Central Office, where data forms and electronic files will be securely stored (in locked filing cabinets or relational databases on password-protected computers). Data will be entered using form based entry systems, to ensure data quality. Automated data checking will be used to identify outliers and improbable data, and if data quality appears to be poor as a result of automated procedures, site data verification may be considered in a subset of centres.

#### Withdrawal

Only those women who sign a consent form and return the questionnaire at 10-12 days will be sent the three month questionnaire. Non-respondents will be deemed to have withdrawn. Where women respond at 10-12 days but not at three months, a reminder will be issued. If they fail to respond to the reminder they will be deemed to have withdrawn. In addition, participants may withdraw at any time by contacting the PEARLS Central Office. Reasons for withdrawal will be sought in this instance, but women will not be required to give details if they choose not to.

### Statistical issues

#### Sample size

In a clustered design, due consideration needs to be made of the fact that there are certain factors pertaining to the cluster (maternity unit), as well as to the individual, which can affect outcome measures, and hence the sample size depends not only on the size of difference one wishes to detect, but also the intra-cluster correlation coefficient (ICC) [15]. Typically such values are small, and it is very unlikely that the ICC will exceed 0.05. The sample size calculation for the trial assumes that at 10 - 12 days 75% of women have any pain whilst walking or sitting in the past 24 hours, that the ICC is 0.013, a 1% significance level, and a cluster size of 40. With 16 clusters (8 pairs) this would give the study 95% power to detect a 20% reduction in primary outcome from 75% to 55% (as seen in the trial by Kettle et al 2002 [7]) or alternatively a small-to-moderate difference of one third of a standard deviation on continuous scales, such as VAS scores for pain). This calculation assumes 0 correlation between paired clusters. Assuming a response rate of 60%, implies recruiting 67 women in each cluster. Having additional clusters will help to preserve sample size should clusters withdraw from the study.

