### Data analysis

The analysis of this trial will be by 'intention to treat', in that we will attempt to include all clusters in the analysis regardless of implementation of the intervention, and attempt to get completed questionnaires returned from all women recruited in each cluster. A 5% 2-sided significance level will be used. Analysis of the primary and secondary outcomes, following the early intervention (i.e in phase 2), will be by means of the matched-pair random effects model [15] and analysed using a multi-level model framework [16] with MLWin software [17]. In this way the paired cluster design is taken into account. Results will be presented graphically as Forest plots to show the variation of effect size between cluster pairs. This framework permits extending the analyses to include individual level and paired-cluster level (such as cluster size, and baseline compliance with RCOG guidelines) variables as covariates. Multilevel models will be used to assess whether the effect of the intervention persists by looking in addition at the data following the second period of intervention. The proportion of eligible women who completed questionnaires will be calculated for each cluster and the intervention groups compared.

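### The 95% power claimed for a difference of one third of a standard deviation does not follow from the stated inputs; at the 1% level they give about 80%

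*Protocol article*

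**What the plan says.** The Sample size section of the protocol article makes one power statement for two kinds of outcome. The assumptions are "that the ICC is 0.013", with "a 1% significance level, and a cluster size of 40". On the matching it adds: "This calculation assumes 0 correlation between paired clusters". For the binary primary outcome it then states "With 16 clusters (8 pairs) this would give the study 95% power to detect a 20% reduction in primary outcome from 75% to 55" per cent. The same sentence continues "or alternatively a small-to-moderate difference of one third of a standard deviation on continuous scales, such as VAS scores for pain". No separate ICC, significance level or power is given for the continuous outcome, so the 95% and the 1% apply to it as well.

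The cluster size is already net of non-response: "Assuming a response rate of 60%, implies recruiting 67 women in each cluster" (40/0.60 = 66.7).

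The sample-size paragraph does not say whether the 1% level is one- or two-sided. The Data analysis section says "A 5% 2-sided significance level will be used".

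**The concern.** The sentence treats a 20-point fall and a difference of one third of an SD as alternatives with equal power. Expressed in SD units, the 20-point fall is clearly the larger effect, so the two cannot both have 95% power with the same clusters, ICC and significance level. One figure must be wrong.

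The clause tells readers what the trial can say about continuous outcomes and names VAS pain scores as the example. Severity of perineal pain is the first secondary outcome listed. The outcome list does not name the scale, so the link to a VAS is a natural reading rather than an explicit statement. A reader who accepts 95% power would take a null result on such a scale as near-exclusion of a small-to-moderate effect. If the true power is lower, that reading is not justified.

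**Working it through.** **Inputs (Sample size section unless noted)**
- 8 clusters per arm, 40 analysed women each: 320 per arm
- ICC 0.013
- Significance level 1%, taken as two-sided in line with the Data analysis section
- Pair correlation 0, so matching gives no gain in precision
- Effects: 75% vs 55%; one third of an SD

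**Design effect**

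DE = 1 + (m − 1) × ICC = 1 + 39 × 0.013 = 1.507. Effective sample size per arm = 320/1.507 = 212.3.

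**The plan's binary figure**

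SE = sqrt[(0.75 × 0.25 + 0.55 × 0.45)/212.3] = sqrt(0.435/212.3) = 0.0453. Then 0.20/0.0453 = 4.42, and power = Φ(4.42 − 2.576) = 96.7% (96.3% with a pooled variance under the null). The stated 95% is reproduced within 2 points, which supports this reading of the inputs.

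**Comparing the two effects**

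Average binary variance = 0.435/2 = 0.2175, so the SD is 0.466. The 20-point fall is 0.20/0.466 = 0.43 SD, against 0.33 SD for the alternative.

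**Power for one third of an SD**

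SE in SD units = sqrt(2/212.3) = sqrt(2 × 1.507/320) = 0.0971. Ratio = 0.3333/0.0971 = 3.43.
- Two-sided 1%: Φ(3.43 − 2.576) = 80.5%
- Two-sided 5%: Φ(3.43 − 1.96) = 93.0%

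**Detectable difference**
- 95% power, 1%: (2.576 + 1.645) × 0.0971 = 0.41 SD
- 80% power, 1%: (2.576 + 0.842) × 0.0971 = 0.33 SD
- 95% power, 5%: (1.960 + 1.645) × 0.0971 = 0.35 SD

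So one third of an SD is what this design detects with 80% power at 1%.

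**Can another reading give 95%?**

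| Reading | Power for 1/3 SD |
|---|---|
| One-sided 1% | 86.6% |
| Two-sided 5% | 93.0% |
| One-sided 5% | 96.3% |
| 10 pairs of 40, two-sided 1% | 89.7% |
| 8 pairs of 67 (full response), two-sided 1% | 92.3% |
| 10 pairs of 67 (full response), two-sided 1% | 97.1% |
| Pair correlation 1, two-sided 1% | 95.2% |
| No clustering (ICC 0), two-sided 1% | 94.96% |

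The rows that reach 95% each contradict a stated input. The last matches the stated figure almost exactly: without clustering, SE = sqrt(2/320) = 0.0791, the ratio is 4.22, and Φ(4.22 − 2.576) = 95.0%. This suggests that the design effect was applied to the binary calculation but not to the continuous one. That origin is an inference; the error itself does not depend on it.

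**Small number of clusters**

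The normal approximation is the favourable case. With 8 pairs, a noncentral t gives, for one third of an SD, 67% (14 df, unpaired) or 52% (7 df, paired) at 1%, and 89% or 84% at 5%.

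**What the stated claim would need**

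One third of an SD at 95% power and 1% needs 2 × (2.576 + 1.645)² × 9 = 321 women per arm before clustering. Multiplied by 1.507 this is about 484, or 12.1 clusters of 40 per arm: 13 per arm after rounding up, instead of 8.

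**The case against.** The arithmetic on the stated inputs is not in dispute. The case on the other side is that little follows from it.

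1. **Analysis level.** The Data analysis section tests at a two-sided 5%. There, power for one third of an SD is 93.0% and the detectable difference at 95% power is 0.35 SD, close to what is claimed. This stands as a limit on the consequence: the miss risk is 7% at 5%, and the roughly fourfold excess (19.5% against 5%) applies only at 1%. It does not rescue the sentence, which uses 1% and whose binary figure reproduces at 1%.
2. **More clusters are planned.** The Study design section sets a minimum of 20 units. Ten pairs of 40 give 97.0% at 5% and 89.7% at 1% (normal approximation). This also softens the consequence, but the claim is made for 8 pairs, and the Sample size section presents the extra clusters as a reserve against withdrawal. Even with all ten pairs, 1% does not give 95%.
3. **Degrees of freedom.** The protocol article fixes none, and with zero pair correlation 14 df is as defensible as 7. This is accepted. The t-based figures show direction only, and the finding does not rest on them.
4. **Secondary status.** The clause is an aside; the sample size is driven by the binary primary outcome, whose power statement is sound. That is correct and lowers the weight of the point. It leaves a published power figure that the design does not deliver.

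**Conclusion.** The statement is wrong as written. At the 1% level it uses, the design has about 80% power for one third of an SD, 14.5 points below the stated 95%; equivalently, 95% power is reached at 0.41 SD. This rests on the protocol's own inputs, a two-sided test, the normal approximation, and the stated ICC applying to the continuous scale as well, since no other is given. Power falls as the ICC rises: at 0.05, which the protocol considers very unlikely to be exceeded, it is about 45% at 1%.

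The practical weight is modest. The primary-outcome power stands, no recruitment target changes, and at a two-sided 5% level the shortfall is about 2 points under the normal approximation. What needs correcting is the assurance given about continuous outcomes.

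**What to change.** Replace the clause on continuous scales with the figure that the design delivers. If the 1% level is kept: 95% power for a difference of 0.41 SD, or about 80% power for one third of an SD. If the calculation is moved to the 5% level of the Data analysis section: 93% power for one third of an SD. Say in either case that the level is two-sided and that the figures include the design effect of 1.507 and use the normal approximation. A t-based value next to these would help readers, given so few clusters, but is optional.

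The cost is one rewritten clause and a less favourable stated power for continuous outcomes. Sample size, recruitment and analysis do not change. Keeping 95% power for one third of an SD at 1% would instead need 13 clusters of 40 per arm, which a secondary power remark does not justify.

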### Data analysis

The analysis of this trial will be by 'intention to treat', in that we will attempt to include all clusters in the analysis regardless of implementation of the intervention, and attempt to get completed questionnaires returned from all women recruited in each cluster. A 5% 2-sided significance level will be used. Analysis of the primary and secondary outcomes, following the early intervention (i.e in phase 2), will be by means of the matched-pair random effects model [15] and analysed using a multi-level model framework [16] with MLWin software [17]. In this way the paired cluster design is taken into account. Results will be presented graphically as Forest plots to show the variation of effect size between cluster pairs. This framework permits extending the analyses to include individual level and paired-cluster level (such as cluster size, and baseline compliance with RCOG guidelines) variables as covariates. Multilevel models will be used to assess whether the effect of the intervention persists by looking in addition at the data following the second period of intervention. The proportion of eligible women who completed questionnaires will be calculated for each cluster and the intervention groups compared.

### Ethical considerations and Safety Committee

The protocol has been approved by the Thames Valley ethics committee. The conduct of the trial will be according to the principles of *MRC Guidelines for Good Clinical Practice in Clinical Trials *(1998) [18] and the appropriate NHS Research Governance Frameworks. All participating units will be required to sign an *Investigator's Agreement*, detailing their commitment to accrual, compliance, Good Clinical Practice, confidentiality and publication. Deviations from the agreement will be monitored and the Project Steering Committee will decide whether any action needs to be taken, e.g. withdrawal of funding, suspension of centre.

Site Specific R&D approval is required for each participating unit, whereby the NHS Trust Research and Development (R&D) Office will assess "locality issues" relating to the local population, investigators, facilities and resources. In order to comply with current arrangements, an employee of each unit (this could be the appointed local training facilitator) would have to assume responsibility as the local 'Principal Investigator', assisting the project team with procedures to obtain local R&D approval requirements for research governance. The PEARLS Central Office will help Principal Investigators obtain local R&D approval. The local Principal Investigator will be responsible for liaison with the local Trust management team regarding locality issues, and must obtain the necessary signatures from their Trust. Once local R&D approval have been granted and evidence provided to the PEARLS Central Office, the local Principal Investigator will receive a folder containing all the necessary materials to allow the trial to commence in their unit.

It is unlikely that the introduction of a training package in perineal care will cause any adverse reactions amongst women. However, any serious unexpected adverse events (SAEs) believed to be due to perineal suturing will be reported to the study office as soon as possible. This should be followed within 7 days by a completed SAE form. Events that might reasonably be expected to occur in women following childbirth do not need to be reported. For the purposes of this study, "serious" adverse events are those which are fatal, life-threatening, disabling or require hospitalisation, either for the mother, or the baby. "Unexpected" adverse experiences are defined as those that would not be expected among women following childbirth. An independent Data Monitoring and Ethics Committee (DMEC) will be convened, which will consider accumulating data from this and other studies, and advise the chair of the Trial Steering Committee if, in their view, there is both a) 'proof beyond reasonable doubt' that for all, or for some women or centres, the training package is definitely indicated or contra-indicated in terms of a net difference in the major endpoints, and b) evidence that might reasonably be expected to influence the management of women, the TSC can then decide whether to close or modify any part of the study. Unless this happens, however the central project team, the steering committee, the investigators and all of the central administrative staff (except the statisticians who supply the confidential analyses) will remain unaware of the interim results.

## Conclusions

This is the first RCT to quantify an evidence-based, 'hands on' training package to enhance the assessment and management of childbirth associated perineal trauma. It is likely to collect the largest data set to date on aspects of clinical management and women's health outcomes following birth related perineal trauma. A reduction in maternal morbidity as a consequence of enhanced clinical training has implications for practice and women's health globally.
